#### Study feasibility and experience

We record adherence to interventions and assessments, missing data, and adverse events. At the end of the intervention period and at study completion, participants complete exit surveys that query acceptability of interventions and assessments. The exit surveys also include questions related to any physical activity performed outside of intervention sessions and between intervention completion and retention testing. We also intend to develop a complementary qualitative study of participant and exercise professional experiences and perceptions of delivery of task-oriented exercise programming to PwMS with specific consideration of initial impairment level (i.e., PDDS of 3–4 and PDDS of 5–6).

#### Adverse events

Any adverse events will be self-reported by the participants and/or reported by exercise professionals and study personnel. Adverse events will be reported to the Institutional Research Ethics Board as required and assessed by the study team for seriousness, expectedness and causality following the guidelines of the National Health and Medical Research Council position statement for monitoring and reporting of safety for clinical trials [69].

#### Statistical analysis and sample size calculation

Baseline data collection will include both demographic and MS-related information (Table 3). The primary statistical analysis will compare T25-FWT performance at the post-intervention time point between the three study arms using ANCOVA (analysis of covariance) with a between-groups factor (task-oriented, generalized resistance and aerobic exercise, stretching control) and adjusting for baseline T25-FWT performance [28]. Planned pairwise comparisons will directly test differences between each study arm. Comparison of the secondary outcome and all other outcome measures at the post-intervention time point across study arms will follow the primary analysis methods (i.e., ANCOVA adjusting for relevant baseline measure). Exploratory analysis of change in outcome measures across all time points and between study arms will use a linear mixed effects model with Time point, Study arm, and Baseline T25-FWT performance as fixed factors. Participant will be a random factor. The models will account for dependencies/correlations resulting from repeated measurements. Final exploratory analyses will re-run all statistical tests with data disaggregated by sex [70–72]. For all statistical tests, the alpha will be 0.05. Point and 95% confidence interval estimates for study arm differences will be determined. Participants will be analyzed in the study arm to which they were randomized (i.e., intention-to-treat principle). Multiple imputation will be used to minimize biased estimates from missing data with the analysis based on a missing at random assumption [73]. We will conduct an interim analysis when 50% of the sample has completed study procedures. This interim analysis will allow dissemination (i.e., conference presentations) of preliminary findings. There is no stopping rule for the trial because no serious adverse events from the intervention are anticipated.

**Table 3 Tab3:** Baseline data collection variables

Variables
Age (years)
Sex
Gender (optional)
Height
Weight
BMI
Type of MS
Year of MS onset (e.g., first symptom)
Year of MS diagnosis (by a neurologist)
Most recent relapse (month/year)
Patient Determined Disease Steps
Walking aid or assistive devices
More affected side (upper and lower body)
Medications (including disease-modifying therapy)
29-Item Multiple Sclerosis Impact Scale
Clinical MRI availability
Other health conditions
Employment/Work status
Typical Day
Fall history past 7 days
Fall history complete/triggers
Godin Physical Activity/Leisure Questionnaire
TMS contraindications

Notes: BMI: body mass index; MS: multiple sclerosis; MRI: magnetic resonance imaging; TMS: transcranial magnetic stimulation

The sample size was calculated based on the primary hypothesis and outcome. Most prior work studying the effects of exercise on walking speed has used interventions that cannot be distinctly classified as task- or non-task-oriented exercise, and has not compared the effects of different types of exercise [21, 22]. Thus, our sample size calculation is informed by a study in which combined gait and dual-task training resulted in a greater improvement in walking speed than lower-extremity resistance exercise in PwMS [28]. The combined gait and dual-task training (n = 26) yielded an average improvement in walking speed of 21.4%, while the resistance exercise (n = 12) yielded only a 2.5% change (i.e., null) [28]. The effect size describing the difference between groups in change in walking speed was large and significant (Cohen’s d = 0.95, 95% CI: 0.2–1.7) [28]. As the proposed intervention is longer and of higher volume than the prior work [28], we expect an effect size of similar or greater magnitude. Thus, based on the effect size reported in the prior work [28], we determined that a total of 63 participants (n = 21 per study arm) will be required to detect a clinically important mean difference of 20% in walking speed on the T25-FWT [59, 74] between study arms at the post-intervention time point with a two-sided significance level of 5%, a power of 85%, and equal allocation to the three arms of the trial.

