**Methods:**

This study is a single-blinded, three-arm randomized controlled trial conducted in Saskatchewan, Canada. Eligible participants are those older than 18 years of age with a diagnosis of MS and an expanded Patient-Determined Disease Steps (PDDS) score between 3 (‘gait disability’) and 6 (‘bilateral support’). Exercise interventions are delivered for 12 weeks (3 × 60-min per week) in-person under the supervision of a qualified exercise professional. Interventions differ in exercise approach, such that task-oriented exercise involves weight-bearing, walking-specific activities, while generalized resistance and aerobic exercise uses seated machine-based resistance training of major upper and lower body muscle groups and recumbent cycling, and the stretching control exercise involves seated flexibility and relaxation activities. Participants are allocated to interventions using blocked randomization that stratifies by PDDS (mild: 3–4; moderate: 5–6). Assessments are conducted at baseline, post-intervention, and at a six-week retention time point. The primary and secondary outcome measures are the Timed 25-Foot Walk Test and corticospinal excitability for the tibialis anterior muscles determined using transcranial magnetic stimulation (TMS), respectively. Tertiary outcomes include assessments of balance, additional TMS measures, blood biomarkers of neural health and inflammation, and measures of cardiorespiratory and musculoskeletal fitness.

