### Study arm allocation

All consenting participants who have completed a baseline assessment are stratified into either a mild (PDDS of 3–4) or moderate (PDDS of 5–6) impairment category. Participants from each strata are then randomly allocated to one of the three study arms: task-oriented exercise, generalized resistance and aerobic exercise, or stretching control. Allocation is completed by an administrative assistant not involved in data collection or analyses. Randomization lists were computer-generated in small blocks to help achieve balance across groups. The randomization list was created prior to participant recruitment by a research team member not involved in data collection or analyses.

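### Randomization is stratified by PDDS category, but no ANCOVA or mixed model in the plan includes the stratum, so reported standard errors may be somewhat too large

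*Protocol article*

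**What the plan says.** **Allocation.** Under Study arm allocation, the Protocol article says that participants with a completed baseline assessment are "stratified into either a mild (PDDS of 3–4) or moderate (PDDS of 5–6) impairment category" and are then randomized within stratum to the three arms. It adds: "Randomization lists were computer-generated in small blocks to help achieve balance across groups". The abstract also describes blocked randomization stratified by PDDS.

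**Analysis.** Statistical analysis and sample size calculation names the model terms:

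- Primary outcome: "ANCOVA (analysis of covariance) with a between-groups factor (task-oriented, generalized resistance and aerobic exercise, stretching control) and adjusting for baseline T25-FWT performance".
- Secondary and all other outcomes: these "will follow the primary analysis methods (i.e., ANCOVA adjusting for relevant baseline measure".
- Exploratory mixed model: "Time point, Study arm, and Baseline T25-FWT performance as fixed factors", with participant as a random factor.

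PDDS is in none of these lists. Elsewhere it is an eligibility criterion, a baseline variable, a clinical assessment, the rule for workload increments in the maximal exercise test, and a focus of the planned qualitative work. No quantitative analysis adjusts for it.

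**The concern.** Stratified blocks force the arms to be nearly equal in PDDS category, which removes one source of between-arm variation from the treatment comparison. A model without the stratum leaves that variation in the residual, so its standard error describes a less balanced trial than the one that was run. If PDDS carries prognostic information that the baseline covariate does not, intervals are wider than they should be, the test runs below its nominal level, and some power is lost.

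The protocol article lists the covariates of each model, so this is a matter of what it fixes and not of detail left to a fuller document. With 21 participants per arm there is little precision to spare. In the ANCOVAs for active motor threshold, blood markers and fitness, the only covariate is the outcome's own baseline, so walking impairment enters only indirectly.

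**Working it through.** **1. The plan's sample size.** Inputs from the sample size paragraph: Cohen's d = 0.95 and "a two-sided significance level of 5%, a power of 85%, and equal allocation to the three arms of the trial". For one pair of arms, the normal approximation gives n = 2(1.960 + 1.036)² / 0.95² = 19.9, so 20 per arm. The noncentral t calculation gives 83.3% power at 20 per arm and 85.2% at 21. The stated 21 per arm, 63 in total, is reproduced without the stratum in the model.

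**2. Degrees of freedom.** The primary ANCOVA estimates an intercept, two arm contrasts and one baseline slope: 63 − 4 = 59 residual degrees of freedom. With the stratum, 63 − 5 = 58.

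**3. Reported interval width.** Let g be the share of outcome variance remaining after the baseline covariate that PDDS category explains. The documents do not give g. I assume 0 to 0.15. Including the stratum multiplies the reported standard error by √(1 − g):

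- g = 0: 1.000, no narrowing
- g = 0.05: 0.975, 2.5% narrower
- g = 0.10: 0.949, 5.1% narrower
- g = 0.15: 0.922, 7.8% narrower

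**4. Simulation of the design.** Settings taken from the article: 63 participants, three arms, permuted blocks within two PDDS strata, and ANCOVA on arm and baseline. One pairwise contrast was tested at two-sided 0.05, in line with "For all statistical tests, the alpha will be 0.05". Assumptions, because the article gives no figures: half of participants in each stratum, blocks of six, correlation of PDDS category with baseline T25-FWT of 0.5 or 0.7, residual SD of 1, and d = 0.95 applied on that residual scale. There were 15,000 null and 6,000 alternative replicates per setting. Each cell gives the results for correlation 0.5 / 0.7.

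| g | Model SE, omitted | Empirical SE, omitted | Model SE, included | Type I, omitted | Type I, included | Power, omitted | Power, included |
|---|---|---|---|---|---|---|---|
| 0 | 0.309 / 0.309 | 0.311 / 0.310 | 0.310 / 0.310 | 0.053 / 0.050 | 0.053 / 0.049 | 0.854 / 0.860 | 0.853 / 0.854 |
| 0.05 | 0.310 / 0.309 | 0.303 / 0.306 | 0.303 / 0.302 | 0.046 / 0.049 | 0.050 / 0.050 | 0.867 / 0.861 | 0.875 / 0.873 |
| 0.10 | 0.310 / 0.309 | 0.299 / 0.302 | 0.294 / 0.294 | 0.042 / 0.044 | 0.050 / 0.049 | 0.855 / 0.861 | 0.877 / 0.884 |
| 0.20 | 0.311 / 0.310 | 0.289 / 0.298 | 0.278 / 0.277 | 0.036 / 0.040 | 0.049 / 0.052 | 0.865 / 0.874 | 0.916 / 0.924 |

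The value g = 0.15 was not simulated; the last two rows bracket it. Monte Carlo error is about √(0.05 × 0.95 / 15,000) = 0.002 for type I error and √(0.86 × 0.14 / 6,000) = 0.004 for power. The 0.053 at g = 0 is therefore noise, and it appears with the stratum included as well.

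**5. Reading the results.** The simulated ratio at g = 0.10, 0.294 / 0.310 = 0.948, agrees with step 3. At that value the gap between the two model standard errors is 0.310 − 0.294 = 0.016 (correlation 0.5) or 0.309 − 0.294 = 0.015 (0.7). Of this, 0.310 − 0.299 = 0.011 or 0.309 − 0.302 = 0.007 is overstatement in the reported standard error. The rest is a real difference in the precision of the estimate. So roughly half to two thirds of the gap is a reporting error.

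**The case against.** The strongest objection is that the harm is conditional and may be close to nil. PDDS 3–6 grades gait disability and the T25-FWT times walking, so a continuous baseline T25-FWT plausibly carries most of what a two-level PDDS category could add. At g = 0 nothing is lost by omission. The omission is never anti-conservative, and the planned 85% power does not rely on the stratum. All of this stands, and it limits the size of the point.

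Three stronger readings are tempting, and the documents do not support them:

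- A reader might infer that precision is certainly being lost. That requires g above zero, and the article has no figure bearing on g.
- A reader might turn the narrower intervals into extra participants: at g = 0.15, 63 × (1 / 0.85 − 1) = 11. That equates reported interval width with information. Stratified allocation already improves the estimate even when the model ignores it, as the empirical standard errors show, so the figure overstates what is lost. At g = 0 it is zero.
- A reader might infer that PDDS was chosen because it was expected to predict walking. The article does not say so. Its stated aim for the small blocks is balance across groups.

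For the other outcomes, each ANCOVA adjusts for its own baseline, and nothing in the article shows that PDDS adds to that. The stratum could matter more or less there than for walking.

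**Conclusion.** The point holds as a mismatch between randomization and analysis with a known direction and an uncertain, probably modest, size. The stratum is absent from every model whose terms the article lists. If PDDS category predicts outcome beyond the baseline covariate, reported standard errors are too large and tests conservative. There is no bias and no type I inflation.

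Over an assumed 0–15% of residual variance, reported intervals would be about 0–8% narrower with the stratum included. Power, omitted versus included, is about 0.86 versus 0.85 at 0% and 0.86 versus 0.88 at 10%; type I error at 10% is about 0.043 when the stratum is omitted. These figures rest on the simulation assumptions above, chiefly the unknown g. Confidence is high in the omission and its direction, and low in the size of the loss. The point does not threaten the trial's conclusions, but the improvement is almost free.

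**What to change.** Add the randomization stratum (PDDS 3–4 versus 5–6) as a fixed effect in the primary ANCOVA, in the ANCOVAs for the secondary and other outcomes, and in the exploratory mixed model. The article does not specify the imputation model, and that is no fault here; once the stratum is in the analysis models, the imputation model should contain it too for consistency. The change is best recorded before any comparison of outcomes by arm, including the interim analysis planned at 50% of the sample.

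The cost is one phrase in each model statement and one residual degree of freedom, 59 to 58 in the primary ANCOVA. The sample size stays at 63.

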### Outcome measures

All outcomes are assessed at baseline, after completion of the 12-week intervention, and at a six-week retention time point (Table 2). At each time point, outcome measures are collected across three separate assessment sessions within a seven-day period. A study team member schedules the sessions and contacts participants 24 h prior to the first of the three sessions as a reminder. The assessment sessions include: (1) All clinical assessments conducted in a 90-minute session, (2) TMS and fitness-based measures obtained in a two-hour session, and (3) Blood samples collected in a 30-minute session.

**Table 2 Tab2:** Schedule of study enrolment, intervention and assessments

	Study period					
	Enrollment	Allocation	Baseline A_x_	Intervention	Post A_x_	Retention A_x_
Time point		Week 0	Week 0	Weeks 1–12	Week 13	Week 18

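### The exploratory mixed model lists no arm × time term, so as written it gives no contrast for differential change or for retention

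*Protocol article*

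**What the plan says.** In the section on statistical analysis and sample size, the protocol article describes the model's purpose as "Exploratory analysis of change in outcome measures across all time points and between study arms". The model is a "linear mixed effects model with Time point, Study arm, and Baseline T25-FWT performance as fixed factors", and "Participant will be a random factor". The text adds that correlation between repeated measurements will be handled. It names no interaction.

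The Outcome measures section fixes the visits: "All outcomes are assessed at baseline, after completion of the 12-week intervention, and at a six-week retention time point". Table 2 places them at weeks 0, 13 and 18, so baseline is one of three time points.

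The primary analysis is an ANCOVA of T25-FWT at post-intervention, adjusted for baseline T25-FWT. The sentence just before the mixed model extends this to the secondary and all other outcomes, again at post-intervention only, as "ANCOVA adjusting for relevant baseline measure". The mixed model is therefore the only stated analysis that uses the retention visit, apart from its planned repetition by sex.

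**The concern.** The stated purpose is to see whether change differs by arm. A model with main effects of arm and time has no parameter for that. It assumes that the difference between any two arms is the same at every visit, including baseline, where randomisation makes the expected difference zero.

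Two further features stand out. The covariate is baseline T25-FWT for every outcome, so motor threshold, blood markers, balance and fitness would be adjusted for their own baseline in the ANCOVA and for walking time in the mixed model. And when T25-FWT is itself the outcome, the baseline value is both a response and a covariate if all three visits are modelled.

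At stake is what the trial can say about week 18. The Background faults earlier studies for not evaluating follow-up effects, and the Discussion offers more persistent benefit as plausible. Every outcome is measured again at retention, but the listed terms would not show whether a gain was kept, and the single arm coefficient could be misread as the treatment effect.

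**Working it through.** **1. The plan's own figure.** The mixed model has no stated figure, so the only one to reproduce is the sample size: "a total of 63 participants (n = 21 per study arm) will be required", from "Cohen’s d = 0.95, 95% CI: 0.2–1.7", "with a two-sided significance level of 5%, a power of 85%, and equal allocation to the three arms of the trial". For two arms the normal approximation gives n = 2(1.960 + 1.036)² / 0.95² = 19.9, so 20 per arm and 60 in all. The t-based calculation gives 20.9, so 21 per arm and 63 in all, with power 0.852. The stated figure is reproduced and does not depend on the mixed model. The 0.95 SD effect is used below for illustration.

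**2. The model as listed.** For participant i at visit j:

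Y(ij) = μ + α(arm) + τ(visit) + β·B(i) + u(i) + e(ij)

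where B is baseline T25-FWT. The expected change from baseline to post-intervention is τ(post) − τ(base) in every arm, so differential change is zero by construction. The arm difference is one number for all visits.

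**3. What that number estimates.** Let the true arm difference be 0 at baseline, δ at post-intervention and rδ at retention, where r is the share retained. With complete, balanced data the expected arm coefficient is:

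- three visits as responses: (0 + δ + rδ)/3 = δ(1 + r)/3
- post-intervention and retention only: (δ + rδ)/2 = δ(1 + r)/2

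**4. Numbers, with δ = −0.95 SD** (a negative sign means a shorter walking time). Simulated values are means over 4,000 trials with 21 per arm, SD 1 and within-person correlation 0.7. The SD and correlation are assumptions, not in the document; with balanced complete data the expected coefficients do not depend on the correlation.

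| Retained share r | Three visits: formula | Simulated | Share of δ | Two visits: formula | Simulated | Share of δ |
|---|---|---|---|---|---|---|
| 1 | −0.633 | −0.635 | 67% | −0.950 | −0.953 | 100% |
| 0.5 | −0.475 | −0.474 | 50% | −0.7125 | −0.712 | 75% |
| 0 | −0.317 | −0.317 | 33% | −0.475 | −0.476 | 50% |

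In both layouts the same coefficient can arise from different combinations of δ and r, so it cannot separate a large effect that was lost from a smaller one that was kept.

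**5. With arm × time added** (contrast at post-intervention / at retention):

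| r | True | Three visits, baseline also a covariate | Two visits, baseline as covariate |
|---|---|---|---|
| 1 | −0.95 / −0.95 | −0.953 / −0.954 | −0.952 / −0.953 |
| 0.5 | −0.95 / −0.475 | −0.951 / −0.473 | −0.950 / −0.473 |
| 0 | −0.95 / 0 | −0.953 / −0.002 | −0.952 / −0.001 |

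Both contrasts are recovered, even where baseline is on both sides of the model. The covariate is constant across a participant's visits, so it drops out of the within-participant change. Double use of baseline is therefore redundant, but does not bias the change contrasts once the interaction is present.

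**6. The covariate for other outcomes.** This was reasoned through, not simulated. Baseline T25-FWT is measured before allocation, so its expected difference between arms is zero and adjusting for it does not bias an arm contrast. It will usually explain less of another outcome's variance than that outcome's own baseline does, so the cost is precision. The conflict with the own-baseline rule is plain from the two adjacent sentences.

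**The case against.** The strongest reply is that the sentence is a condensed list of factors in a journal article, not a model formula. Its stated aim, change between arms, points towards an interaction, and a full analysis plan that is not shown may include one. Nowhere does the text say main effects only. This stands as a limit on certainty: the point concerns what is written, and the intention may have been sound. It does not dispose of the matter. The sentence sets out the fixed terms, and the interaction is the one term its aim requires. The baseline T25-FWT covariate is a positive statement that disagrees with the sentence before it, so this is more than missing detail.

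A second reply is that dilution depends on reading baseline as a response row. That also stands. The reference to all time points favours three visits, but naming a baseline covariate is compatible with follow-up visits only, and then nothing is lost at full retention. Both ranges are therefore given.

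A third reply is that the analysis is exploratory, that no stated hypothesis concerns retention, and that the Discussion raises persistence among limitations. All of this is correct and sets the severity.

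**Conclusion.** The point holds, with moderate severity. Run as written, the model gives one visit-averaged arm coefficient: 67%, 50% or 33% of the post-intervention effect with baseline as a response row, or 100%, 75% or 50% without it, at full, half or no retention. It gives no contrast for differential change or retention. These figures assume complete balanced data, no arm difference at baseline in expectation, and the fixed terms taken literally.

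Three stronger readings are tempting and are not supported:

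- A reader might infer that the trial's main conclusion is at risk. The primary and secondary outcomes are baseline-to-post changes analysed by ANCOVA, and neither those analyses nor the sample of 63 involves this model.
- A reader might infer that the covariate and the double use of baseline also prevent estimation of change. Only the absent interaction does that. The covariate costs precision and consistency, and the double use is redundant.
- A reader might infer that the effect is always diluted. With follow-up rows only and full retention, it is not.

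**What to change.** Amend the mixed-model sentence to include study arm × time point, and state that the arm contrasts at post-intervention and at retention will be reported with 95% confidence intervals. Then choose one layout:

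- post-intervention and retention values as responses, with each outcome's own baseline as covariate; or
- all three visits as responses, with no baseline covariate, and the contrasts expressed as differences in change from baseline.

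Either layout removes the conflict with the ANCOVA rule and the double use of baseline. The planned repetition by sex should use the same corrected model. Further terms, such as baseline × time or the PDDS stratum, are not needed to cure this fault.

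The cost is a short text change. With three arms, the interaction adds (3 − 1)(2 − 1) = 2 parameters in the first layout and (3 − 1)(3 − 1) = 4 in the second. No new data are needed, and the sample size stays at 63.

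### The exploratory sex analysis repeats every test within each sex and has no arm-by-sex term, so it contains no valid estimate or test of whether arm effects differ by sex

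*Protocol article*

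**What the plan says.** All of this is in the protocol article, section on statistical analysis and sample size calculation, unless noted.

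- Sex analysis: "Final exploratory analyses will re-run all statistical tests with data disaggregated by sex".
- Significance level: "For all statistical tests, the alpha will be 0.05".
- Primary model: an ANCOVA with an arm factor, "adjusting for baseline T25-FWT performance". Other outcomes follow the same approach, each with its own baseline. "Planned pairwise comparisons will directly test differences between each study arm".
- Longitudinal model: a "linear mixed effects model with Time point, Study arm, and Baseline T25-FWT performance as fixed factors".
- Estimates: "Point and 95% confidence interval estimates for study arm differences will be determined".
- Sample size: "a total of 63 participants (n = 21 per study arm) will be required", from an effect size of "Cohen’s d = 0.95, 95% CI: 0.2–1.7", with two-sided 5% significance and 85% power.

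Sex is collected at baseline (Table 3). Randomization is stratified by PDDS only (section on study arm allocation). The expected proportion of women is not given. None of the hypotheses at the end of the Background concerns sex.

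**The concern.** Whether an arm effect differs by sex is a question about a difference between two differences. Separate tests in women and in men each ask whether the arm effect differs from zero in that sex, and neither asks whether the two effects differ from each other. A significant result beside a non-significant one can arise simply because both subsets are small or one is smaller than the other.

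The design makes this likely. The sample size covers the whole-sample pairwise comparison only, so each sex has well under the planned power, and sex is not balanced by design. With no arm-by-sex term, the plan offers a reader nothing else from which to judge effect modification. At stake is an unsupported sex-specific message about which exercise suits whom. The main trial result is not at stake.

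**Working it through.** **Inputs.** From the article: d = 0.95 (CI 0.2 to 1.7), two-sided alpha 0.05, 21 per arm, three arms. Assumed: the split by sex, taken as 11:10, 14:7, 15:6 or 16:5 in every arm, and the same true d in both sexes. As in the protocol's own calculation, d is treated as the standardized effect in the analysis, with no further gain from baseline adjustment.

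**1. Reproduce the plan's figure.** Two-sample t-test with n per arm: df = 2n − 2, noncentrality = d√(n/2). For n = 21: df = 40, noncentrality = 0.95 × √10.5 = 3.08, critical t = 2.02, power 85.2%. Solving for 85% power gives n = 20.90, rounded up to 21. The stated 63 is reproduced.

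**2. Power within each sex, same formula.** Write p₁ and p₂ for the power in the larger and smaller sex. With independent subsets, P(exactly one significant) = p₁(1 − p₂) + p₂(1 − p₁). Example at 14:7 and d = 0.95: 0.677 × 0.627 + 0.373 × 0.323 = 0.424 + 0.120, about 0.545.

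| Split per arm | Power at d = 0.95 | Exactly one sex | Both | Neither |
|---|---|---|---|---|
| 11:10 | 56%, 52% | 50% | 29% | 21% |
| 14:7 | 68%, 37% | 55% | 25% | 20% |
| 15:6 | 71%, 32% | 58% | 23% | 20% |
| 16:5 | 74%, 26% | 61% | 20% | 19% |

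**3. Vary the effect.** The protocol's own CI for d is wide, so one value is not enough. Exactly one sex significant, same true effect in both, over the four splits:

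| Common d | Exactly one sex |
|---|---|
| 0 | 9.5% |
| 0.2 | about 13% |
| 0.5 | 31–33% |
| 0.95 | 50–61% |
| 1.7 | 8–35% |

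The pattern is commonest at moderate to large effects. It falls when power is low in both sexes, or high in both.

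**4. Compare with an interaction contrast.** A simulation of the three-arm layout (20,000 runs per scenario, variance pooled over arms, no baseline covariate) agrees with step 2: 49%, 54%, 57% and 60% at d = 0.95. In the same runs, a contrast of the arm difference in women with that in men, at alpha 0.05, was falsely significant in 4.9–5.3%.

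**5. What the interaction can and cannot show.** In SD units its standard error is √(2/n₁ + 2/n₂): √(2/11 + 2/10) = 0.62 at 11:10 and √(2/16 + 2/5) = 0.72 at 16:5. With 63 − 6 = 57 residual df (critical t about 2.00), the 95% CI half-width is about 1.24 to 1.45 SD. Simulated power is 33% (11:10) down to 25% (16:5), even if the effect is 0.95 in the larger sex and 0 in the other.

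**6. Number of tests.** Each original test is kept and repeated in two sexes: 1 + 2 = 3 times the original number, all at 0.05.

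**The case against.** The strongest reply is that the article never says a sex difference will be inferred from the separate results. It announces disaggregated analyses, calls them exploratory, states no sex hypothesis, and plans 95% CIs for arm differences. Sex-specific estimates with CIs are legitimate reporting. All of this stands. A reader might infer that the authors intend to declare sex differences from one-sided significance, or that the trial is likely to reach a spurious conclusion. The text supports neither: the percentages above are frequencies of a pattern of p-values, not of a conclusion drawn. What remains is that the planned CIs are for arm differences, and none is for the difference between the sexes.

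A second reply is that the detail may sit in an unseen analysis plan. But the article does name a method, repeated testing by sex, and that method cannot answer the comparison. An added interaction model would be compatible with the sentence, but it is not stated.

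Third, the size depends on assumptions. The sex split is not in the documents, d could lie anywhere in a wide interval, and the planned ANCOVA may be more precise than an unadjusted t-test. That is fair, and is why ranges are given.

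Fourth, a single model assumes a common baseline slope and residual variance across the sexes, which separate fits do not. That is a real trade-off, so separate fitting is not in itself an error. Dropping within-sex p-values or limiting the analysis to the main outcomes would be a matter of preference and is not asked for here.

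**Conclusion.** The point holds as a limited one. The sex analysis, as fixed in the article, has no valid estimate or test of effect modification, and its separate tests invite a misleading reading. With identical true effects, a given pairwise comparison is significant in exactly one sex in about half or more of trials at the design effect (50–61%), in about a third at d = 0.5 (31–33%), and in 8–35% at d = 1.7, against about 5% false signals from an interaction contrast. These figures rest on splits of 11:10 to 16:5 in every arm, a common d and an unadjusted t-test. The defect in method does not depend on them. The analysis is exploratory, and the primary ANCOVA, its pairwise comparisons and the sample size are untouched.

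**What to change.** For the exploratory sex analysis, fit the ANCOVA, and likewise the mixed model, on all participants with sex and arm-by-sex terms added. Report the interaction estimate with its 95% CI, together with the sex-specific arm differences and their 95% CIs from the same model. Label the sex-specific results descriptive, and state that no sex difference will be claimed from significance in one sex alone.

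The cost is a sentence or two in the analysis plan and no new data, since sex is already recorded. The drawback is imprecision: with about 25–33% power even against a complete absence of effect in one sex, a non-significant interaction must not be presented as evidence of equal effects. The plan should say so.
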